#### Assessment of cases and controls

All of the tests listed below: mMRC, the COPD Assessment Test (CAT) [16], the Hospital Anxiety and Depression Scale (HADS) [48], the WHO Fracture Risk Assessment Tool (FRAX) [49], and a 3-level version of the EuroQol 5-dimensional descriptive system (the EQ-5D-3 L) [50–52] will be offered to all cases and controls.

#### Symptoms

The mMRC scale uses a simple grading system to assess a patient's level of dyspnea (0, patient only becomes breathless with strenuous exercise; 1, patient becomes short of breath when hurrying on level ground or walking up a slight hill; 2, on level ground, patient walks slower than people of the same age due to breathlessness or must stop for breath when walking at his/her own pace; 3, patient stops for breath after walking approximately 100 m or after a few minutes on level ground; or 4, patient is too breathless to leave the house or he/she is breathless when dressing). The CAT test is a validated, short (8-item) and simple patient-completed questionnaire that displays adequate discriminatory properties that was developed for use in routine clinical practice to measure the health status of patients with COPD [53]. The CAT test is scored in a range of 0 to 40. A CAT test score greater than or equal to 10 indicates a high level of symptoms, and an mMRC scale score greater than or equal to 2 indicates pronounced dyspnea [1].

#### Psychosocial measurements

The HADS is used to determine the levels of anxiety and depression experienced by the patients [48]. The score for each subscale (anxiety and depression) ranges from 0 to 21, and these scores are categorized as follows: normal (0-7), mild (8-10), moderate (11-14), and severe (15-21). Scores for the entire scale (emotional distress) range from 0 to 42; higher scores indicate greater distress.

#### Fracture risk

The FRAX was used to evaluate the fracture risk of patients [49]. The FRAX algorithm computes the 10-year probability of a fracture. FRAX considers the following risk factors: age, sex, previous fracture, parent fractured hip, current smoking, glucocorticoid use, rheumatoid arthritis, secondary osteoporosis, and 3 or more alcohol units consumed per day. A unit of alcohol is equivalent to a standard glass of beer (285 ml), a single serving of a spirit (30 ml), a medium-sized glass of wine (120 ml), or 1 serving of an aperitif (60 ml).

#### Quality of life

A 3-level version of the EuroQol 5-dimensional descriptive system (the EQ-5D-3 L) was used as a standardized measure of health status [50–52]. The EQ-5D-3 L consists of 2 instruments: the EQ-5D descriptive system and the EQ visual analog scale (EQ VAS). The EQ-5D-3 L descriptive system assesses the following 5 dimensions: mobility, self-care, typical activities, pain/discomfort and anxiety/depression. Each item is scored according to 3 levels: no problems, some problems and extreme problems. The respondent is asked to indicate his/her health state by selecting the box that corresponds to the most appropriate statement in each of the 5 dimensions. The EQ VAS records the respondent’s self-rated health on a vertical, visual analog scale in which the endpoints are labeled “best imaginable health state” and “worst imaginable health state”. This information can be used as a quantitative measure of health outcome as judged by the individual respondents [52].

#### Laboratory testing

Blood samples were collected from all patients exhibiting AL after fasting (between 7:00 AM and 10:30 AM) and were immediately stored in a refrigerated container until arrival at the central laboratory (<3 h after blood collection). Plasma (EDTA, heparin) or serum samples were obtained after centrifugation. A hemogram, including counts of red (RBCs) and white blood cells (WBCs) and leukocytes, was immediately performed at one of 2 laboratories (in St. Petersburg and Arkhangelsk) upon arrival. Aliquots of serum were stored in a freezer at -80° for subsequent analysis at the central lab in St. Petersburg. Mucosal swabs were collected and frozen for future gene analysis.

The following laboratory tests will be performed on all cases and controls: blood counts (WBCs and RBCs), the levels of cholesterol, triglyceride, creatinine, glucose, AST, ALT, high-sensitivity C-reactive protein (hs-CRP), IL-4, IL-6, IL-8, IL-10, TNFα, Clara cell protein, SP-D, vitamin D protein, MMP-9, TIMP-1, and α1-antitrypsin, and genetics (DNA from buccal swab for the identification of polymorphic variants of the RIN3, MMP12, and TGFB2 genes). In 30 cases and 30 controls, induced sputum will be examined for the concentrations of neutrophils, lymphocytes, eosinophils, CC16, IL-8, TNFα and immunoglobulin (IgG).

### Study III (an ongoing prospective cohort study with two years of follow-up)

#### Study population

All newly identified individuals with an FEV_1_/FVC of less than 0.7 or less than the LLN before and/or after the reversibility test were included in the cohort study. All diagnosed cases exhibiting irreversible AL (FEV_1_ < 200 ml and 12 % after bronchodilation) were subsequently identified.

After the initial assessment of each participant in this cohort (baseline (T0) and examination by pulmonologist (T1)), two follow-up visits are scheduled: one year (T2) and two years (T3) after the initial visit.

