**Discussion:**

In total, 3133 individuals (2122 from St. Petersburg and 1012 from Arkhangelsk) aged 35–70 years agreed to participate in this study and met the inclusion criteria. In total, 2974 participants met the quality criteria for spirometry, and 2388 reversibility tests were performed. A cohort of newly defined obstructive pulmonary disease patients (247 persons) was established for follow-up investigation.

The RESPECT study will provide information regarding the prevalence of COPD in the north-west region of the Russian Federation. Moreover, the comprehensive RESPECT database will enable us to explore new research questions, provide novel insight into the risk factors and different phenotypes of COPD, and contribute to an improved understanding of the reasons why some heavy smokers develop the disease whereas others do not.

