The aim of our study is to gain a better understanding of the prevalence, pathogenesis and symptoms of early COPD. This study seeks to address the following specific objectives/research questions: 1) to estimate the prevalence of AL and COPD in adults 35-70 years of age in St. Petersburg and Arkhangelsk based on sex, age, environmental conditions, socioeconomic status and smoking status; 2) to compare the prevalence of COPD in the study population based on the GOLD and LLN criteria; 3) to identify the diagnostic value of various signs, symptoms and background characteristics for the diagnosis of COPD; 4) to determine whether differences in background characteristics, inflammatory biomarkers and pneumoproteins are evident between smokers with and without COPD; and 5) to describe co-morbidity, functionality and global health status in a cohort of newly diagnosed COPD patients.

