### Study II (case-control study)

#### Study population and sample size

One hundred patients with COPD and a smoking history of more than 10 pack-years (cases) and one hundred patients with the same smoking history without COPD (controls) will be invited in the second study in order to reach the needed sample size of 2 × 70 patients.

The inclusion criteria for the cases and the controls include the following: 1) a smoking history of more than 10 pack-years and 2) age between 35 and 70 years.

The cases and the controls will be matched based on the following criteria: age group, sex, smoking history, level of pollution in living area, body mass index, comorbidity (cardio-vascular diseases index, systemic disease, and tuberculosis in anamnesis), and use of medications that may influence the inflammatory status.

The cases will include 100 participants that meet the following criteria: 1) smokers aged 35–70 years with a smoking history of >10 pack-years; 2) completely irreversible AL based on the following criteria: FEV_1_/FVC < 0.7 according to the GOLD criteria (fixed threshold) or FEV_1_/FVC < LLN; 3) COPD of stage II-IV according to the GOLD criteria (post-bronchodilation FEV_1_ < 80 % of the predicted value) or the LLN criteria (FEV_1_ below the LLN); and 4) a confirmed diagnosis of COPD by a pulmonologist after a comprehensive clinical examination.

The controls will include 100 participants based on the following criteria: 1) smokers aged 35–70 years with a smoking history of >10 pack-years and without COPD according to the GOLD or LLN criteria, 2) without asthma (absence of symptoms), 3) no history of allergies, and 4) free from the use of bronchodilators.

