## Results

Participants aged 35-70 years from the patient list from each center were selected using a random number generator; initially, 4419 individuals were invited to participate in the study. In total, 3133 individuals agreed to participate and met the inclusion criteria. In addition, 2974 participants demonstrated satisfactory quality on spirometry (after comprehensive quality assessment for reproducibility and acceptability) (Fig. 2). Basic spirometry analysis revealed 247 participants with obstructions before bronchodilation (FEV_1_/FVC < 0.7). Good-quality bronchodilator tests were obtained from 2388 participants. Of these participants, 162 were patients with AL (FEV_1_/FVC < 0.7), including 130 patients with irreversible lung obstruction (FEV_1_ < 200 ml or 12 % after bronchodilation).

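### Irreversible airflow limitation is defined in conflicting ways, and the follow-up cohort of 247 fits neither its entry rule nor its COPD label

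*Protocol article*

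**What the plan says.** **Irreversibility.** The term appears in three places, all current text:

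- Study III, Study population: irreversible cases are those with "FEV_1_ < 200 ml and 12 % after bronchodilation".
- Results: "130 patients with irreversible lung obstruction (FEV_1_ < 200 ml or 12 % after bronchodilation".
- Study II, Study population and sample size, second case criterion: "completely irreversible AL based on the following criteria: FEV_1_/FVC < 0.7 according to the GOLD criteria (fixed threshold) or FEV_1_/FVC < LLN". It gives no reversibility threshold and does not say whether the ratio is taken before or after bronchodilation.

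**The cohort.** The Abstract (Discussion) says: "A cohort of newly defined obstructive pulmonary disease patients (247 persons) was established for follow-up investigation". The Results say where that number arises: "Basic spirometry analysis revealed 247 participants with obstructions before bronchodilation", with the fixed 0.7 cut-off. The entry rule is given in the Abstract (Methods/Design), in Study III under Study population, and under Assessment of patients with AL. It admits a ratio below 0.7 or below the LLN, before and/or after bronchodilation. The Discussion (COPD diagnosis) adds that people with borderline values but no obstruction also entered the cohort.

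**The label.** Objective 5, at the end of the Background, places its outcomes "in a cohort of newly diagnosed COPD patients". Two aims in the Conclusion also call the cohort COPD.

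**The concern.** A classification term used in two of the three component studies has no single meaning, and the one count reported for it (130) rests on wording that the Study III section contradicts. Study II seeks 100 cases. If its irreversibility criterion is meant to carry the FEV1-change rule, the choice between *and* and *or* affects who qualifies, before the pack-year and severity criteria narrow the pool further.

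The cohort raises a different problem. Its reported size matches one narrow criterion (fixed ratio, before bronchodilation), its entry rule is wider, and its label is a diagnosis. Co-morbidity, functional status, phenotypes and progression would be reported as findings in COPD for a group in which a substantial part has no documented post-bronchodilator obstruction. A reader could not tell which people the results describe.

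**Working it through.** **1. The plan's own prevalence figure.** Sample size calculations: n = Z²P(1 − P)/d² with Z = 1.96, P = 0.08, d = 0.01. This gives 3.8416 × 0.0736 / 0.0001 = 2827.4, rounded up to 2828, as stated. The article prints counts of 247, 162 and 130 but no COPD percentage.

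**2. *And* against *or*.** Read literally, both thresholds apply to FEV1 itself. I read them as limits on the gain in FEV1 after bronchodilation. The two limits coincide at a baseline FEV1 of 200/0.12 = 1667 ml; on either side of it the rules can disagree. Illustrative patients (not from the article):

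| Baseline FEV1 | Gain | Gain, % | Irreversible under *and* | Irreversible under *or* |
|---|---|---|---|---|
| 2000 ml | 100 ml | 5 | yes | yes |
| 2500 ml | 250 ml | 10 | no | yes |
| 1000 ml | 150 ml | 15 | no | yes |
| 2000 ml | 300 ml | 15 | no | no |

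Everyone irreversible under *and* is also irreversible under *or*. If 130 is the *or* count, the *and* count is at most 130. The *or* rule sets aside 162 − 130 = 32 of 162 (19.8%); *and* would set aside at least 32. No second count or individual data are given, so the gap cannot be computed.

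**3. Cohort size against entry rule.**

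| Route into the cohort | In the entry text? | In the count of 247? |
|---|---|---|
| Ratio < 0.7 before bronchodilation | yes | yes |
| Ratio < LLN only | yes | no |
| Obstruction only after bronchodilation | yes | no |
| Borderline, no obstruction | Discussion only | no |

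The figure 247 can equal the cohort size only if the last three routes added nobody or were offset by people who did not enter. The article says neither.

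**4. Documented post-bronchodilator obstruction.** The Results give 2388 good-quality bronchodilator tests and 162 people with AL among them, without saying outright that the 162 had a post-bronchodilator ratio below 0.7.

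- If they did, at most 162 of the 247 have documented post-bronchodilator obstruction.
- If instead they are pre-bronchodilator cases who had a usable test, the other 85 have no usable post-test, and again at most 162 can have it documented.

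Either way the minimum without it is 247 − 162 = 85, and 85/247 = 34.4%.

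**5. Denominators.** Taking the 2388 as a subset of the 2974 with acceptable spirometry, 2974 − 2388 = 586 (19.7%) have no good-quality bronchodilator test.

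| Count | Of 2974 | Of 2388 |
|---|---|---|
| 247, obstruction before bronchodilation | 8.31% | not applicable |
| 162, AL among those tested | 5.45% | 6.78% |
| 130, irreversible under *or* | 4.37% | 5.44% |

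The article does not say which row and column its COPD prevalence will use.

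**The case against.** The FEV1-change rule does less work than it first seems. AL is defined by ratio cut-offs alone (Equipment). Entry to Study III is by ratio, and irreversible cases are picked out afterwards, so the *and*/*or* conflict does not decide cohort membership. Study II also requires a post-bronchodilation FEV1 criterion or an LLN criterion, plus a pulmonologist's confirmation. Every cohort entrant is examined by a pulmonologist, spirometry is repeated at T1 to T3, and a consensus diagnosis follows (Future investigations). All of this stands and limits clinical misclassification. It does not make the definitions agree or explain the count of 247.

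Two stronger readings are tempting, and the article does not support them.

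- A reader might infer that the *and*/*or* conflict makes COPD prevalence range from 5.4% to 8.3%. It does not. That spread comes from the stage of testing, the removal of 32 patients and a change of denominator from 2974 to 2388. Only one irreversible count is printed, so the conflict contributes nothing computable to it. The Results call the three counts obstruction, AL and irreversible obstruction, not COPD, and objective 1 names AL and COPD separately. For the same reason the spread should not be set against the ±1 point sampling precision.
- A reader might infer that a third of the cohort may not have COPD. The 85 mix people without a usable post-test with people who were tested and not obstructed. As an illustration only: if the overall 19.7% untested rate held among the 247, about 49 would be untested. If all 162 were also post-bronchodilator cases within the 247, about 36 (15%) would be tested without AL. The true split is not given.

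A detailed prevalence analysis may also sit in a fuller document. That excuses missing detail, but not conflicting statements in this one.

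**Conclusion.** The point holds as two separate inconsistencies, both wrong as written.

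First, irreversible AL is defined with *and* in Study III, with *or* in the Results, and by ratio alone in Study II. The effect on the 130 runs in one direction if *or* was the rule used (130 or fewer under *and*), and its size is unknown. If *or* is only a slip of wording and 130 was tabulated under *and*, the count stands and the Results text is what needs correcting.

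Second, the cohort of 247 is the pre-bronchodilator fixed-ratio count. It matches neither the entry rule nor the addition of borderline participants, yet the cohort is called COPD. At least 85 of the 247 (34%) lack documented post-bronchodilator obstruction.

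This rests on reading the 200 ml and 12% thresholds as limits on FEV1 change, and on the 247 in the Abstract and in the Results being the same people. The minimum of 85 holds under either reading of the 162.

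**What to change.** 1. Reconcile the irreversibility wording in Study II, Study III and the Results to one rule, written as a change in FEV1. State whether the Study II ratio is taken before or after bronchodilation. Re-tabulate the 130 if the rule kept is not the one used to produce it. Which rule to keep is for the investigators.
2. Reconcile the Abstract, the Study III entry rule, the Results and the Discussion (COPD diagnosis). Restate the cohort size under the actual entry rule, with a count for each route: fixed ratio, LLN only, obstruction only after bronchodilation, and borderline if those participants remain.
3. Label the cohort as airflow limitation. Restrict results labelled COPD to participants who meet the study's single reconciled COPD definition. Report those obstructed only before bronchodilation, and those without a good-quality post-test, separately.
4. State the numerator and denominator for COPD prevalence, including how the 586 without a good-quality bronchodilator test are handled.

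The cost is wording and re-tabulation of data already collected. The downside is a smaller group for analyses labelled COPD, of a size that the article does not give.

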#### Assessment of patients with AL

All newly detected individuals displaying an FEV_1_/FVC less than 0.7 or less than the LLN before and/or after the reversibility test are examined using a comprehensive standardized protocol by one of the two principal investigator both experienced pulmonologists.

#### Symptoms and additional variables

Evaluation of the symptoms was based on the mMRC scale [17] and the CAT [16].

The following parameters were assessed at inclusion: risk factors (smoking, occupational hazards and family history of obstructive lung disease); the history of hospitalization and treatment; obstructive disease exacerbation frequency; current known diseases; family anamnesis; a standardized physical examination that includes lung and heart auscultation; measurements of height, weight, BMI, waist circumference, pulse, respiratory rate and blood pressure; and skin and edema assessments.

#### Co-morbidity

The presence/absence of the following diseases was systematically recorded: asthma, allergic disease, chronic bronchitis or emphysema, bronchiectasis, sinusitis, arterial hypertension, ischemic heart disease, heart failure, diabetes, cerebrovascular or peripheral artery disease, depression, cancer, osteoporosis, arthritis, peptic ulcer disease, hepatitis, cirrhosis, kidney disease, and previous myocardial infarction, pulmonary embolism and stroke.

#### Additional assessments

The same measurements were performed to all: the HADS to determine the levels of anxiety and depression [48], the FRAX to evaluate the fracture risk [50] and the EQ-5D-3 L [51–53] to measure the quality of life.

#### Spirometry

For all patients exhibiting AL, a spirometry test was performed during the comprehensive assessment (T1) within a 6-month interval after inclusion in the cross-sectional study (T0) and will be subsequently performed 12 and 24 months after the first examination (T2, T3).

#### Laboratory testing

The following laboratory tests will be performed: WBC count, RBC count, and the levels of cholesterol, triglyceride, glucose, AST, ALT, creatinine, fibrinogen, TNFα, IL-4, IL-6, IL-8, IL-10, hs-CRP, Clara cell protein and SP-D. During the first (initial) visit the following lab parameters will be investigated: Nt-proBNP, vitamin D protein, MMP-9, TIMP-1 and α1-antitrypsin.

#### Future investigations

All participants will be invited for follow-up investigations.

Multispiral computer tomography (CT) and pulmonary functional tests will be offered to a subset of patients (priority given to patients with stage I-II COPD). Newly identified obstructive lung disease patients will be offered body plethysmography to determine total lung capacity (TLC).

After the baseline assessment (T0) and the follow-up examination, a consensus clinical diagnosis will be attained, and both assessments (T1, T2) will be used as an initial and final “reference standard” in the diagnostic study.

### Statistical analysis

All data are stored in a central database. SPSS version 20.0 (SPSS Inc., Chicago, IL, USA) will be used for data analysis. The analyses will include cross-sectional and prospective approaches. Prospective analyses will be performed on the entire cohort. The outcome measures will be registered for every patient who underwent at least one module of the assessment. The variety of dimensions included in the RESPECT will enable us to correct for a wide range of factors in the analyses and multivariate models.

Using bivariate and multivariate analyses correlates for COPD and potential confounders for COPD prevalence (by comparing the COPD prevalence between the GOLD and LLN criteria) will be investigated. Furthermore, various clinical phenotypes of COPD (based on clustering analysis) will be considered.

Future analysis and publications using this cohort will be performed according to the STROBE criteria [54].

### Ethics

All participants provided informed consent. The local medical ethics review boards (North-West State Medical University named after I.I. Mechnikov, St. Petersburg, protocol N 11 from 07.12.2011, and Northern State Medical University, Arkhangelsk, RF, protocol N 01/1-12 from 11.01.2012) approved these studies.

## Results

Participants aged 35-70 years from the patient list from each center were selected using a random number generator; initially, 4419 individuals were invited to participate in the study. In total, 3133 individuals agreed to participate and met the inclusion criteria. In addition, 2974 participants demonstrated satisfactory quality on spirometry (after comprehensive quality assessment for reproducibility and acceptability) (Fig. 2). Basic spirometry analysis revealed 247 participants with obstructions before bronchodilation (FEV_1_/FVC < 0.7). Good-quality bronchodilator tests were obtained from 2388 participants. Of these participants, 162 were patients with AL (FEV_1_/FVC < 0.7), including 130 patients with irreversible lung obstruction (FEV_1_ < 200 ml or 12 % after bronchodilation).

**Fig. 2 Fig2:**
[figure not shown]
RESPECT Flow Diagram

The age and sex distribution of the total RESPECT population is presented in Fig. 3. The background characteristics of the RESPECT population based on sex are presented in Table 1. The mean age of the sample population was 54 years (SD 9.25), and 31.8 % of the RESPECT population was male. No significant differences were detected in the age groups or in the overall socio-economic status between men and women. In total, 73.3 % of men and 35.9 % of women were current or ex-smokers (*P* < 0.05). Women smoked for a shorter duration than men (21.1 years, SD 11.9 versus 28.4 years, SD 12.9, *P* < 0.05). Men more frequently reported exposure to occupational hazards than women (38.7 and 24.9 %, respectively, worked at a dusty job; 37.4 and 21.9 %, respectively, exposed to gas or chemical fumes, *P* < 0.05). Asthma was indicated as a current known disease (according to the patient) more often by women, whereas men more frequently reported emphysema (*P* < 0.05). Cough and sputum > three months was more frequently reported by men than by women (22.7 and 18.0 %, respectively, *P* < 0.05), whereas dyspnea was indicated more often by women (9.2 %, *P* < 0.05).

